## 7.0 STUDY DESIGN

This will be a prospective open multicentre randomised controlled trial in patients with higher risk non ST elevation myocardial infarction acute coronary syndrome.

### 7.1 AIMS OF THE STUDY

This study will aim to answer the following questions:

- In N-STEMI ACS patients who are shown to be at higher-risk (GRACE score  $\geq 118$  or  $\geq 90$  with additional high risk features), does immediate angiography with a view to follow on revascularisation significantly improve outcomes (efficacy and safety) compared to angiography with follow on revascularisation at routinely used timing?
- Will any benefits correlate with degree of estimated risk (i.e. will the highest GRACE 2.0 score patient benefit most)?
- Is an early intervention strategy cost effective?
- Can mechanistic understanding be gained from CMR sub-study?
- Can novel biomarkers predict need for PCI and future clinical outcomes?
- Will longer term “passive” follow up through NHS Digital show an improvement in outcomes?

### 7.2 OUTCOME MEASURES (for definitions see APPENDIX II)

#### 7.2.1 Primary clinical outcome

Incidence of the composite of **all-cause mortality, new myocardial infarction and admission for heart failure** within **12 months** following randomisation.

#### 7.2.2 Secondary Outcome Measures

- Individual components of the primary end-point within 12 months:
  - Incidence of all-cause mortality within 12 months
  - Incidence of new myocardial infarction within 12 months
  - Incidence of admission for heart failure within 12 months
- Incidence of cardiovascular mortality within 12 months
- Length of in-patient stay (defined as randomisation to first discharge) in days
- Events prior to planned procedure:
  - Incidence of all-cause mortality prior to planned coronary angiography following index admission with NSTEMI
  - Incidence of new myocardial infarction prior to planned coronary angiography following index admission with NSTEMI
  - Incidence of major bleeding (classified as BARC 3-5) prior to planned coronary angiography following index admission with NSTEMI
- Incidence of admission for ischaemia-driven revascularisation within 12 months
- Incidence of admission for any cause within 12 months
- Quality of life measured using Seattle angina score at 24 hours post procedure, 1 month, 6 months and 12 months
- Quality of life as assessed using the EQ-5D-5L questionnaire at 24 hours post procedure, 1 month, 6 months and 12 months
- Incidence of BARC 3-5 classified bleeding as in-patient, and up to 12 months
- Incidence of stroke within 12 months

RAPID-NSTEMI[figure not shown]

- Cost effectiveness of immediate PCI versus standard care
- Left ventricular ejection fraction (LVEF) and infarct size on cardiac MRI scan\*
- Sensitivity and specificity of novel biomarkers in predicting which patients do or do not require PCI following diagnostic angiography\*\*
- Proportion of patients needing emergency/urgent revascularisation (in group B)
- Incidence of total VARC-2 classified access site complications as in-patient, and up to 12 months
- Incidence of major VARC-2 classified access site complications as in-patient, and up to 12 months

\*Additional CMR outcomes are specified in the CMR substudy protocol (appendix V)

\*\* Additional biomarker outcomes are specified in the Biomarkers substudy protocol (appendix VI)

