#### 7.3.2 Exclusion Criteria

- ST elevation myocardial infarction
- Evident type 2 myocardial infarction (e.g. anaemia)
- Evidence of previous known cardiomyopathy
- Cardiogenic Shock
- Known severe valvular heart disease
- Need for urgent PCI according to ESC Guidelines (haemodynamic instability, VT/VF, recurrent or persistent pain)
- Any contraindication to PCI
- Current participation in another intervention trial

RAPID-NSTEMI

[figure not shown]

Figure 2: Patient Flow to Randomisation

[figure not shown]

\*or written consent, depending on local regulatory guidelines (applicable to sites in Northern Ireland/Scotland only)

RAPID-NSTEMI[figure not shown]**7.4 TRIAL INTERVENTIONS**

If the initial clinical eligibility for N-STEMI criteria are suspected, blood is drawn for Hs-Troponin immediately (i.e. as close to admission as possible). If this returns raised according to individual hospitals criteria then a GRACE 2.0 score is calculated at that time. A GRACE 2.0 score of  $\geq 118$ , or  $\geq 90$  with additional high risk features - see inclusion criteria, will lead to patient ASSENT (or written informed consent, depending on local regulatory guidelines. Further details are provided in section 7.6) and if confirmed then randomisation providing there are no exclusion criteria. If the initial Hs-Troponin is reported as normal, a second sample may be taken at 3 hours in line with current European guidelines. If elevated, the participant may be randomised if all other criteria met. Randomisation will be performed using an independent Interactive Voice Response System randomisation system (Sealed Envelope Ltd), the patient will be randomised to either Group A or B. The participant trial number will be documented.

**GROUP A:** Immediate angiography with follow-on revascularisation if indicated - transfer to the catheter laboratory should be performed as soon as possible, and is recommended but not mandated within 90 minutes of randomisation

**GROUP B:** Standard angiography with follow on revascularisation if indicated, - within Guideline recommended times.  
Standard interim therapy such as LMWH/DAPT will be mandated in this group until angiography.

All interventional procedures will be undertaken according to current best practice (e.g. peri-procedural intravenous heparin, radial approach as preferred access site, and use of drug-eluting stents). Patients in Group B who suffer the following:-

- on-going chest pain,

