- recurrent dynamic ECG changes
- haemodynamic instability during the wait till angiography

will be allowed to cross to earlier angiography +/- revascularisation as per best clinical practice. Reasons for cross-over will be carefully documented. Crossover rates will be carefully monitored for accuracy but if crossover occurs, this will be measured as a secondary end-point.

We have considered carefully whether this design will allow sufficient temporal separation between the two groups enabling robust interpretation of the results. According to the 2015 BCIS audit returns, the median time to angiography for patients (directly) admitted to a PCI-capable centre with N-STEMI ACS = 60.8 hours, and for inter-hospital transfer = 82.1 hrs. Apart for one outlier the earliest time for the direct admission patients appears to be in the order of 26 hours. The risk of time contamination between groups A and B will be minimised by strict trial discipline; without this discipline the study will be difficult to interpret and will not be robust. The “times to intervention” will be important trial audit measures. All recruiting sites will be asked to treat the standard care arm participants according to their

RAPID-NSTEMI[figure not shown]

NHS Trust's current practice. To reduce time delay in Group A only trial sites with on-site cath labs will be included.

All patients will be included in a within-trial cost effectiveness analysis.

A mechanistic CMR sub-study of 200 patients (100 from each group) will evaluate LV function, and differences in infarct size (especially the impact of Type 4a MIs) between groups (APPENDIX V).

A biomarkers substudy will investigate if novel biomarkers can predict the need for PCI and future clinical outcomes (APPENDIX VI)

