**7.15.2 ADVERSE EVENTS**

All adverse events will be collected from randomisation until discharge from hospital. Thereafter only adverse events deemed serious or those listed as an expected SAE's or a pre-specified clinical outcome measure (see section 7.1.5) will be collected until the end of the trial.

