To achieve a power (1-β) of 80% with a (two sided) α=0.05, 964 patients are required in each arm. Assuming up to 5% drop-outs, 5% crossover, 8% needing CABG 1157 patients will be recruited to each of the treatment arms A and B, leading to a total of 2314 patients. (Risks to complete recruitment **APPENDIX VI**).

Based on the above, we consider the power calculations to be conservatively robust and the proposed sample size of sufficient power to detect a significant (and clinically important) reduction in primary endpoint. The calculations have been performed in STATA v14 using the  $\chi^2$  test of equal proportions with the support of the proposed trial statistician.

The trial will follow an adaptive design with closed DSMC review of standard of care event rates.

RAPID-NSTEMI[figure not shown]**8.2 STATISTICAL ANALYSIS PLAN**

Statistical analyses will be undertaken according to a pre-trial Statistical Analysis Plan (SAP) which will be prepared by the statistician employed on the study. Descriptive characteristics at baseline will be presented by treatment arm.

The Primary endpoint is composite outcome of major cardiovascular events (MACE–Death/MI/admission with heart failure) within 12 months, and secondary analyses will be performed for MACE at 30 days following identical methodology. All analyses will be performed following the intention-to-treat principle, with subsequent “immediate follow-on revascularisation” secondary analyses. The primary analysis will investigate the proportion of participants having a primary outcome in each arm, with OR and 95% confidence interval calculation. Additional analyses will compare events in Group A and B with a “time-to-event” endpoint of the primary outcome occurring up until 12 months. Two-sided 95% confidence intervals will be presented for the primary endpoint and all secondary end-point comparisons between groups. The detailed statistical analysis plan will be produced and agreed with the Trial Steering Committee, Sponsors and trial funders prior to trial initiation. The trial will be registered with [clinicaltrials.gov](https://clinicaltrials.gov).

A methods paper outlining the trial will be sent to an appropriate recognised journal for publication.

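### Three secondary outcomes stop counting at angiography, so the allocated arm sets the time at risk and the comparison favours Group A even if timing has no effect

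*Protocol*

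**What the plan says.** Protocol section 7.2.2 groups three secondary outcomes as events before the planned procedure. The one for death reads "Incidence of all-cause mortality prior to planned coronary angiography following index admission with NSTEMI". The one for infarction reads "Incidence of new myocardial infarction prior to planned coronary angiography following index admission with NSTEMI". The one for bleeding reads "Incidence of major bleeding (classified as BARC 3-5) prior to planned coronary angiography following index admission with NSTEMI". None has a fixed end time. None is restricted to one arm, although the same list does restrict another outcome (emergency or urgent revascularisation) to Group B.

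Section 7.4 sets the timing. In Group A, transfer to the catheter laboratory "is recommended but not mandated within 90 minutes of randomisation". For usual care the section cites audit data: "the median time to angiography for patients (directly) admitted to a PCI-capable centre with N-STEMI ACS = 60.8 hours". One outlier aside, the shortest time it gives is about 26 hours. The trial summary prefers Group B angiography by 72 hours.

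Section 8.2 states: "Two-sided 95% confidence intervals will be presented for the primary endpoint and all secondary end-point comparisons between groups".

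Table 1 and Table 2 schedule a pre-angiography troponin in Group B only, and the pre-angiography column of Table 2, which also holds an ECG, is for Group B only.

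A related outcome in 7.2.2 is "Incidence of BARC 3-5 classified bleeding as in-patient, and up to 12 months". The scientific abstract expects length of stay to differ between the arms.

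**The concern.** When an outcome stops being counted at angiography, and the arms differ by design in when angiography happens, the arms are watched for different lengths of time. Group A has fewer countable events simply because its window closes sooner. A between-arm ratio then mixes any true benefit of early angiography with the difference in time at risk, and the definition gives no way to separate them.

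The omitted events matter too. A peri-procedural infarction in Group A at hour 3 falls outside these outcomes, while an infarction in a waiting Group B patient at hour 50 is counted. The protocol itself treats early procedural harm as a live possibility: section 6.0 describes a small trial in which most of the excess with immediate PCI arose in the acute stage, and section 6.2 discusses Type 4a MI at early PCI. Section 6.0 also credits another trial's benefit to re-infarction during the wait, so a result on these outcomes could easily be read as the mechanism of benefit.

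Detection of MI differs as well. Appendix II requires symptoms or new ECG changes plus a biomarker at least 20% above the previous value. Group B has one extra scheduled look at both the ECG and the biomarker inside the window.

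**Working it through.** **The plan's own figure.** The protocol gives no figure for these outcomes. Its sample size reproduces: with 19% v 14.25%, two-sided 0.05 and 80% power, n = [1.960 x sqrt(2 x 0.16625 x 0.83375) + 0.8416 x sqrt(0.19 x 0.81 + 0.1425 x 0.8575)]^2 / 0.0475^2 = 963.2, which rounds up to 964 per arm. The recruited number, 1157 per arm (section 8.1), is used below.

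**Inputs**
- Window in Group A: 1.5 h (section 7.4). Because this is only recommended, 6 h is used as an assumed longer wait.
- Window in Group B: 60.8 h (audit median, direct admissions) and 26 h (shortest time given), both section 7.4.
- Hazard: assumed constant and equal in both arms. Three levels are taken from rates in the protocol: 19% in 12 months (section 8.1), and 4.3% and 13% in 30 days (the two arms of the 323-patient trial in section 6.0).

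**Formula.** Hazard = -ln(1 - risk) / hours. P(event in window w) = 1 - exp(-hazard x w). Expected events = 1157 x P.

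**Risk ratio A/B with no treatment effect.** At these low hazards it is nearly the ratio of the windows:
- 1.5 / 60.8 = 0.025 (about 40 to 1)
- 6 / 60.8 = 0.10
- 6 / 26 = 0.23
- same fixed window in both arms: 1.00, whatever the hazard

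**Expected events and chance of a significant result favouring A, with no effect** (1.5 h v 60.8 h; Fisher's exact test, 4,000 simulated trials):

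| Rate behind the hazard | Hazard per hour | Events A | Events B | Chance p<0.05 favouring A |
|---|---|---|---|---|
| 19% in 12 months | 0.0000241 | 0.04 | 1.7 | under 1% |
| 4.3% in 30 days | 0.0000610 | 0.1 | 4.3 | about 24% |
| 13% in 30 days | 0.000193 | 0.3 | 13.5 | about 98% |

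Worked line for 13%: -ln(0.87)/720 = 0.000193; 1 - exp(-0.000193 x 60.8) = 0.0117; x 1157 = 13.5. If Group A waits 6 h, the last column becomes under 1%, 20% and 89%. As a cross-check, with no event in A the two-sided test needs about six events in B (2 x 0.5^6 = 0.031; five give 0.0625). That explains the steep rise between 1.7 and 13.5 expected events.

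**In-patient bleeding.** The protocol gives no lengths of stay. Assumed stays of 2 v 3, 2 v 4, 3 v 5 and 3 v 3.5 days (A v B) give no-effect risk ratios of 0.67, 0.50, 0.60 and 0.86. At an assumed 5% per 30 days that is at most about 4 extra events in Group B.

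**The case against.** *Shortening the wait is the treatment.* In a strategy trial, counting what happens while patients wait is a legitimate description, and section 8.2 promises intervals, not a claim of benefit. This stands as a case for reporting these events. It does not justify a between-arm ratio. A fixed window from randomisation contains every waiting-period event that falls within it, and adds Group A's procedural events over the same hours.

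*Fixed-window analyses already exist.* The primary outcome, the 12-month components and MACE at 30 days (section 8.2) all count Group A's procedural events. That is true and limits the damage. It does not repair the three comparisons as defined, and no 30-day bleeding comparison is listed.

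*The windows are soft.* The 90 minutes is a recommendation about transfer, and 60.8 h is an audit median applied to every Group B patient. The outcome wording refers to index admission, and section 7.3.1 allows randomisation up to 6 h after it. If the clock ran from admission at that limit, Group A's window would be 7.5 h, giving 7.5/60.8 = 0.12, or 7.5/26 = 0.29. The size moves, but the direction does not.

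*Repeat troponin for recurrent symptoms applies to both arms* (section 7.10). So Group A infarctions are not missed altogether; only the scheduled looks are unequal.

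*The SAP is not shown* and may treat these outcomes descriptively. The definitions, however, are set in the protocol.

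**Conclusion.** The point holds for the three pre-angiography outcomes. With a common hazard, Group A's shorter window cannot give a no-effect ratio above 1, and the ratio equals 1 only if nothing happens between the two angiography times. Under a constant hazard it is about 0.025 to 0.23 for the main range of windows. A hazard concentrated in the first hours would bring it closer to 1. The ratio hardly depends on the hazard level, but event counts and significance depend on it strongly.

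A reader might infer more than the documents support:
- *That a significant result is assured by design.* It is not: the chance runs from under 1% to about 98%. The estimate is biased; significance is not certain.
- *That in-patient VARC-2 access-site complications favour Group A in the same way.* Their risk starts at arterial access, so the relevant span is procedure to discharge, and nothing shows that it is shorter in Group A.
- *That adverse-event collection adds to the bias.* "All adverse events will be collected from randomisation until discharge from hospital" is a collection rule, not a secondary outcome with a promised comparison, and serious events and pre-specified outcomes are still collected after discharge.
- *That the main result is affected.* The primary endpoint and the 12-month outcomes run over a fixed period.

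In-patient bleeding is a minor point. Its direction depends on a shorter stay in Group A, which the protocol implies but does not quantify, and it has a 12-month counterpart.

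**What to change.** In section 7.2.2, make the between-arm comparison death, new MI and BARC 3-5 bleeding from randomisation to fixed times in both arms, whether or not angiography has happened: for example 72 hours or 7 days, and 30 days. Seven days is the safer early choice. Appendix II allows Type 4a MI up to 48 h after PCI, and 60.8 + 48 = 108.8 h, so a 72-hour window would take in Group A's procedural period and cut off part of Group B's.

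Report pre-angiography events descriptively only, or as rates per patient-day at risk. State beside the MI result that Group B has an extra scheduled troponin and ECG, because a fixed window does not remove that difference.

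As a minor change, base the early bleeding comparison on 30 days from randomisation in place of the in-patient period.

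The cost is an amendment to the outcome wording and the matching SAP lines, best made before any comparative data are seen. No new data are needed: the time-to-event analysis in section 8.2 already requires event dates for the composite, bleeding is already an outcome, and the 30-day contact is in section 7.14. A 72-hour cut-off would also need event times; 7 and 30 days need dates only.

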### 7.3 ELIGIBILITY

#### 7.3.1 Inclusion Criteria

- 18 years of age and over
- Patients presenting to hospitals with a clinical diagnosis of non-ST elevation myocardial infarction comprising:
  - Ischaemic symptoms (as defined in Appendix III)
  - Elevated high sensitivity Troponin T or I (above the normal range for individual hospitals)
- GRACE-2.0 score ([www.gracescore.org](http://www.gracescore.org)) of either:
  - $\geq 118$  (corresponding to 6-month death  $>6\%$ ) OR
  - $\geq 90$  but  $<118$  (corresponding to 6-month death  $>3\%$  but  $<6\%$ )
- If GRACE 2.0 score  $\geq 90$  or  $<118$  must have at least one additional high risk feature:
  - Anterior location of ECG changes (leads V2 – V5)
  - ST-segment depression in 2 contiguous leads (any territory) of 0.15mV/ 1.5mm
  - Diabetes Mellitus on medication
  - High-sensitivity Troponin I or T 3 x ULN
- Onset of ischaemic symptoms at any time prior to admission but most recent episode within 12 hours prior to admission
- Intention to perform angiography and, if indicated, follow-on revascularisation
- Provision of assent or written consent
- Randomisation must be performed within 6 hours of admission

#### 7.3.2 Exclusion Criteria

- ST elevation myocardial infarction
- Evident type 2 myocardial infarction (e.g. anaemia)
- Evidence of previous known cardiomyopathy
- Cardiogenic Shock
- Known severe valvular heart disease
- Need for urgent PCI according to ESC Guidelines (haemodynamic instability, VT/VF, recurrent or persistent pain)
- Any contraindication to PCI
- Current participation in another intervention trial

RAPID-NSTEMI

[figure not shown]

Figure 2: Patient Flow to Randomisation

[figure not shown]

\*or written consent, depending on local regulatory guidelines (applicable to sites in Northern Ireland/Scotland only)

RAPID-NSTEMI[figure not shown]**7.4 TRIAL INTERVENTIONS**

If the initial clinical eligibility for N-STEMI criteria are suspected, blood is drawn for Hs-Troponin immediately (i.e. as close to admission as possible). If this returns raised according to individual hospitals criteria then a GRACE 2.0 score is calculated at that time. A GRACE 2.0 score of  $\geq 118$ , or  $\geq 90$  with additional high risk features - see inclusion criteria, will lead to patient ASSENT (or written informed consent, depending on local regulatory guidelines. Further details are provided in section 7.6) and if confirmed then randomisation providing there are no exclusion criteria. If the initial Hs-Troponin is reported as normal, a second sample may be taken at 3 hours in line with current European guidelines. If elevated, the participant may be randomised if all other criteria met. Randomisation will be performed using an independent Interactive Voice Response System randomisation system (Sealed Envelope Ltd), the patient will be randomised to either Group A or B. The participant trial number will be documented.

**GROUP A:** Immediate angiography with follow-on revascularisation if indicated - transfer to the catheter laboratory should be performed as soon as possible, and is recommended but not mandated within 90 minutes of randomisation

**GROUP B:** Standard angiography with follow on revascularisation if indicated, - within Guideline recommended times.  
Standard interim therapy such as LMWH/DAPT will be mandated in this group until angiography.

All interventional procedures will be undertaken according to current best practice (e.g. peri-procedural intravenous heparin, radial approach as preferred access site, and use of drug-eluting stents). Patients in Group B who suffer the following:-

- on-going chest pain,
- recurrent dynamic ECG changes
- haemodynamic instability during the wait till angiography

will be allowed to cross to earlier angiography +/- revascularisation as per best clinical practice. Reasons for cross-over will be carefully documented. Crossover rates will be carefully monitored for accuracy but if crossover occurs, this will be measured as a secondary end-point.

We have considered carefully whether this design will allow sufficient temporal separation between the two groups enabling robust interpretation of the results. According to the 2015 BCIS audit returns, the median time to angiography for patients (directly) admitted to a PCI-capable centre with N-STEMI ACS = 60.8 hours, and for inter-hospital transfer = 82.1 hrs. Apart for one outlier the earliest time for the direct admission patients appears to be in the order of 26 hours. The risk of time contamination between groups A and B will be minimised by strict trial discipline; without this discipline the study will be difficult to interpret and will not be robust. The “times to intervention” will be important trial audit measures. All recruiting sites will be asked to treat the standard care arm participants according to their

RAPID-NSTEMI[figure not shown]

NHS Trust's current practice. To reduce time delay in Group A only trial sites with on-site cath labs will be included.

All patients will be included in a within-trial cost effectiveness analysis.

A mechanistic CMR sub-study of 200 patients (100 from each group) will evaluate LV function, and differences in infarct size (especially the impact of Type 4a MIs) between groups (APPENDIX V).

A biomarkers substudy will investigate if novel biomarkers can predict the need for PCI and future clinical outcomes (APPENDIX VI)

